#### Data management

For the eligible participants, the researcher will collect baseline data at the appropriate time. The primary and secondary outcomes will be assessed by blinded assessors at baseline and 8 weeks (at the end of the intervention). Data will be collected in the case report form (CRF) by the assessors after obtaining signed consent from the patients. Two research assistants who will be blind to the allocation will double-enter and check the data from the CRF. To protect the privacy of the participants, codes and initials will be used instead of their personal information. All of the original data will be stored in ResMan Research Manager of the Clinical Trial Management Public Platform. The relevant research assistants will be trained to ensure that the system meets the trial requirements. In addition, the research manager will oversee clinical data management by monitoring it at least once a week.

#### Quality control

To insure high quality of the trial, all acupuncturists and assessors will undergo strict training before baseline data acquisition to guarantee consistent practices. The training will include diagnoses, inclusion and exclusion criteria, identification of the location of acupoints, acupuncture techniques, and completion of the CRF. The participants will be free to withdraw from the trial at any time for any reason to ensure data authenticity and credibility. Dropouts and withdrawals from the trial will be recorded to ensure an intention-to-treat (ITT) analysis.

In addition, an independent data and safety monitoring team will be established to identify problems, monitor and examine collected data, and control bias once a week. They have the right to suspend the trial or even terminate it at any point if they find any problems or adverse events during the trial. The monitoring team, who should declare no conflict of interest in this study, consists of three members with expertise in different fields: [name] in acupuncture from Shaanxi University of Traditional Chinese Medicine, [name] in statistics, and [name] in insomnia from Shaanxi Provincial Hospital of Chinese Medicine. If there are any problems with regard to the project, the monitoring team will make decisions to alter the details of this protocol and communicate them to the persons conducting the trial by written notice after approval by the application ethics committee.

#### Safety monitoring

Any adverse event, including subcutaneous hematoma, unfavorable or unintended, and fainting, related to acupuncture treatment will be reported by patients and researchers during each acupuncture treatment. In addition, all participants will undergo liver and kidney function examinations, routine blood tests, and stool tests to exclude severe heart/liver/kidney diseases and evaluate the possible side effects of the acupuncture.

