## Background

As a major public health problem, insomnia is defined as sleep difficulties including dissatisfaction with sleep quality, difficulty in initiating or maintaining sleep, and early morning waking, which can affect daytime functioning, and cause fatigue, depression, anxiety, and other symptoms [1, 2]. The prevalence of insomnia is 10–20%, and about 50% of cases involve chronic insomnia, which is defined as suffering from this condition for at least 3 nights each week for 1 month or more [3]. In China, the prevalence of insomnia is approximately 15% [4]. Sleep disturbance is thought to be closely associated with psychological disorders, including depression and anxiety [5]. A survey reported that nearly 30% of the population suffers from psychological disorders due to busy lives and high-pressure jobs, and most affected individuals experience different degrees of insomnia. However, insomnia has not yet been effectively resolved [6, 7].

Medications, such as antidepressants and melatonin, are the most commonly used treatments in the management of insomnia [8]. The use of sleeping pills is common among adults, and middle-aged women with higher education are more likely to have used anti-insomnia drugs [9]. However, adverse effects, including psychological and physical dependence, residual daytime sedation, and cognitive impairment, should not be ignored [10]. Therefore, the American Academy of Sleep Medicine and the American College of Physicians recommend non-pharmacological therapies, including acupuncture and relaxation, first-line treatment options for insomnia [11, 12].

Acupuncture is popular and safe traditional Chinese therapy. It has been used in the treatment of insomnia, depression, and anxiety in China for thousands of years. Acupuncture may restore physiological function through the insertion of needles to stimulate acupoints. Studies have indicated that acupuncture could be effective for sleep disorders by increasing the content of serotonin and aminobutyric acid [13], reducing glutamate levels [14], and improving the function of central inhibition [15]. With better sleep quality, depression and anxiety in patients with insomnia are improved. Previous reviews have shown that acupuncture affects insomnia, but there are no high-quality studies focusing on acupuncture for insomnia, especially for treating depression and anxiety due to insomnia [16, 17].

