**Fig. 1 Fig1:**
[figure not shown]
The study procedure

**Table 1 Tab1:** The trial schedule

Items	Before enrollment (week − 1)	Intervention period (weeks 1–8)	End of intervention (week − 9)
Inclusion criteria	√		
Exclusion criteria	√		
Informed consent	√		
Baseline measurement	√		
Randomization and allocation	√		
PSQI	√		√
Quality of life	√		√
Depression	√		√
Anxiety	√		√
Blinding success rate			√
Adverse events			√

*PSQI* Pittsburgh Sleep Quality Index

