### Blinding

The outcome assessors, data managers, and statistical analysts will be blinded to the treatment allocation. The manual acupuncture and sham acupuncture assignments will be blinded to the patients. The manipulation of needles and acupoints will be similar in both groups. To assess blinding, the participants will be asked whether they experienced manual acupuncture or sham acupuncture after the trial. It will be impossible to blind the acupuncturists because of the characteristics of acupuncture interventions. Unblinding will only be performed in cases of an emergency, such as any serious adverse event.

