### Interventions

All participants will receive 24 sessions of acupuncture (30 min each session, three sessions per week for 8 weeks). Licensed acupuncturists, who have had more than 5 years of clinical experience in acupuncture therapy, will perform the acupuncture treatment. They are well-trained in identifying the locations of the acupoints and the manipulation of needles. The temperature will not be lower than 25 °C in the treatment room. Patients will be allowed to take 0.5–2 mg of Estazolam tablets (Approval number: H37023047, Shandong Xinyi Pharmaceutical Co., Ltd) orally before sleep as a rescue medication. The same acupoints will be used in both groups, including Shenting (GV24), Neiguan (PC6), Shenmen (HT7), Hegu (LI4), Anmian (EX-HN22), Zusanli (ST36), Sanyinjiao (SP6), Zhaohai (KI6), and Shenmai (BL62).

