### Discontinuation

The participants will be free to stop treatment and withdraw from this trial if they are unable or unwilling to complete the treatment, if the scientific research assistant suggests that it would be inappropriate for the patient to continue the study intervention due to a worsening state, or if adverse events, including subcutaneous hematoma, unfavorable or unintended, and fainting, occur during acupuncture treatment. In addition, patients will be advised to contact their doctors in the event of any undesirable effect after the application of acupuncture treatment. The doctor will diagnose and treat the adverse reactions and provide suggestions on whether to continue acupuncture treatment. The participants who are withdraw from the trial will still be followed up and complete the assessments of primary and secondary outcomes.

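### Adverse events must be related to acupuncture to be reported, so rescue-drug harms and events judged unrelated fall outside the stated rule

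*Protocol article*

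**What the plan says.** Five places in the protocol article bear on this.

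- **Safety monitoring** gives the reporting rule: adverse events "related to acupuncture treatment will be reported by patients and researchers during each acupuncture treatment". It adds that "all participants will undergo liver and kidney function examinations, routine blood tests, and stool tests", in order to rule out severe organ disease and to "evaluate the possible side effects of the acupuncture".
- **Interventions** allows estazolam in both arms, taken "orally before sleep as a rescue medication".
- **Background** says of insomnia medication that "adverse effects, including psychological and physical dependence, residual daytime sedation, and cognitive impairment, should not be ignored".
- **Blinding** states: "It will be impossible to blind the acupuncturists because of the characteristics of acupuncture interventions". Patients, outcome assessors, data managers and analysts are blinded.
- **Discontinuation** says that "patients will be advised to contact their doctors in the event of any undesirable effect after the application of acupuncture treatment". The doctor then diagnoses, treats and advises on continuing.

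Table 1 has an adverse-events row. Its only tick is in the column that begins "End of intervention (week − 9". The column for weeks 1–8 is empty.

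**The concern.** A reporting rule should first capture the event and then ask about its cause. Here the question of cause comes first, and an event that fails it need not be written down. Three things follow.

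1. The trial permits a drug from a class whose harms its own Background stresses, yet its adverse-event rule does not ask for those harms. If rescue use differs between arms, a real difference in drug harm could go unrecorded.
2. If the person deciding relatedness knows the arm, the same symptom may be attributed differently after a penetrating needle than after a blunt one. Blinding further down the line cannot correct this.
3. The article describes adverse-event collection in three places that do not fit together, so staff cannot tell when to ask or what to do with an event first reported to a doctor.

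The Discussion hopes to offer a treatment that is safe as well as effective. Any account of adverse events by arm will carry whatever selection the reporting rule imposes. The primary PSQI comparison is not touched by this point.

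**Working it through.** No arithmetic decides this. The check is which events meet the written rule, and whether another part of the article widens it.

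**Step 1: apply the rule to each kind of event.**

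| Kind of event | Within the Safety monitoring rule? |
|---|---|
| Attributed to needling, noticed at the session | Yes |
| Attributed to needling, occurring between sessions | Yes on relatedness; recording depends on its being raised at a later session |
| Attributed to the rescue drug | No, it is not related to acupuncture |
| Judged unrelated to any trial treatment | No |

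**Step 2: see whether other routes widen the rule.**

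- *Laboratory tests.* All participants have them, but the stated aims are to exclude disease and to look for effects of acupuncture. Blood, liver, kidney and stool tests would not show daytime sedation, cognitive impairment or dependence.
- *PSQI.* One of its seven domains scores hypnotic use. That concerns use of the drug, not harm from it.
- *Contact with the doctor (Discontinuation).* This covers any undesirable effect after acupuncture. It is an instruction about care, and the article does not say that such an event enters the case report form.
- *Monitoring team (Quality control).* It examines collected data weekly, and its right to stop the trial over adverse events carries no relatedness condition. It can act only on what reaches it.
- *Table 1.* The end-of-intervention tick is a real collection point apart from the sessions. It gives a time, not a wider definition.

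None of these brings rescue-drug harms or unrelated events into the rule.

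**Step 3: follow the judgement of relatedness.** The reporters are patients, who are blinded, and researchers, who are not further described. The report is made at the session, where the unblinded acupuncturist is treating the patient. Under Data management, blinded assessors complete the case report form and blinded assistants enter the data. If an event is set aside as unrelated before it reaches the form, none of these blinded roles sees it. The Discussion relies on blinding assessors and statisticians to limit detection bias, and that protection starts after this step.

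**Step 4: compare the timings.** Safety monitoring has reporting at every session. Table 1 shows none in weeks 1–8 and one assessment at the end. Discontinuation adds contact at any time with no stated destination. The three descriptions cannot all be followed as written.

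**The case against.** The strongest reply is that too much weight is placed on one loosely worded sentence. Its list of events reads like a shortened form of a longer definition, and the full protocol or the case report form may ask an open question. Table 1 is not a reliable witness either: its weeks 1–8 column is empty in every row, although the Secondary outcomes section places a blinding test at 4 weeks. The empty cell may therefore be careless layout. These points lower confidence about what will happen in practice. They do not remove the problem, because the article states a restriction instead of staying silent, and a fuller document would have to contradict that restriction to cure it.

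Several stronger readings are tempting and are not supported:

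- *Events between sessions are lost.* Patients attend three times a week and can report at one session what happened since the last. Table 1 also has a final assessment, and patients may contact a doctor. Comparing hours spent in sessions with the length of the treatment period says nothing about the share of events captured, because the sentence fixes when events are reported, not when they occur.
- *Relatedness is decided by the unblinded acupuncturist.* The article does not say who decides. Blinded patients also report, and blinded assessors complete the form. Exposure to unblinded judgement is possible, not established.
- *The safety comparison will be wrong.* Adverse events are not listed as a primary or secondary outcome, and the Statistical analysis section describes no between-arm safety test.
- *Every participant takes a hypnotic nightly for 8 weeks and its harms are never recorded.* The article permits rescue use and gives no frequency or duration. Some drug harms may still be written down; the rule simply does not require it.

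**Conclusion.** The point holds in a limited form. As written, the rule excludes harms of the permitted rescue drug and events judged unrelated to acupuncture. It does not state who decides relatedness or whether that person is blinded, so reporting by arm is open to differential attribution. Recording of events between sessions is at risk of being incomplete, and Table 1, Discontinuation and Safety monitoring disagree or leave a gap on when and where events are recorded.

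No size can be given. The article has no figures on adverse-event rates, rescue use by arm, or how often events would be judged unrelated, so neither the amount nor the direction of any distortion is known.

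The conclusion rests on two assumptions: that the Safety monitoring sentence means what it says, and that no fuller document overrides it. The Background lists its harms for insomnia medication in general and does not name estazolam; applying them to the rescue drug is a reading, though a natural one. The change is worth making because it is cheap and improves the safety data. The efficacy design does not depend on it.

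**What to change.** 1. Reword Safety monitoring so that every untoward event is recorded in both arms regardless of suspected cause. Ask one open question at each session about the time since the last one, and ask again at the end-of-intervention visit.
2. Record relatedness as a separate field (acupuncture, rescue drug, other), completed where possible by the existing blinded assessors. No new assessor role is needed.
3. Report all-cause and related events by arm.
4. Enter events that reach a doctor under Discontinuation in the same record.
5. Reconcile Table 1, Discontinuation and Safety monitoring so that they give one schedule and one route.

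This alters data recording only, not treatment or rescue use. The cost is protocol and case report form wording, one question at each of 24 sessions that already take place, and some assessor time for the relatedness field. The downside is more minor, unrelated events to enter.

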#### Statistical analysis

Descriptive characteristics of baseline statistics will be reported as mean ± standard deviation or median. The primary and secondary outcomes will be analyzed based on the ITT. All qualified participants in both groups will receive the intervention and provide outcome assessment at least once. The missing data of participants who drop out will be replaced by the last observation carried forward’ method according to the ITT principle. A two-sample *t*-test or chi-square test will be used to test differences between the manual acupuncture group and sham acupuncture group using SPSS 19.0 by a blinded statistician. All planned tests are two-tailed. Statistical significance will be set at *P* ≤ 0.05.

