### Sample size

Sample size estimation was based on changes in the Pittsburgh Sleep Quality Index (PSQI) score. According to the pre-trial, there was a mean difference in the PSQI of 2.0 with a standard deviation of 4.36 between the two groups. In the current study, we assume a significance level α of 0.05 and power (1-β) = 0.90, owing to which a sample size of 202 can provide effective power to reject the null hypothesis between the manual acupuncture group and sham acupuncture group using two-sided, two-sample *t*-tests assuming equal variance. Considering the expected dropout rate of 20%, this study will require at least 252 participants.

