### Outcomes

#### Primary outcomes

The PSQI, a self-assessment questionnaire used to evaluate sleep quality, will be the primary outcome of this study. It will be administered at baseline and 8 weeks (at the end of the intervention). The PSQI assesses sleep based on seven domains: subjective sleep quality, sleep latency, sleep duration, sleep efficiency, sleep disturbance, hypnotic medication use, and daytime dysfunction. Each domain is rated from 0 to 3, so the total score of the PSQI ranges from 0 to 21. A cutoff score of 5 indicates insomnia [19].

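### With efficacy measured only at baseline and week 8, the LOCF rule is baseline carried forward, which does not fit the 20% dropout allowance and can bias the contrast if missingness differs by arm

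*Protocol article*

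**What the plan says.** All references are to the protocol article.

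- **Missing data (Statistical analysis):** "The missing data of participants who drop out will be replaced by the last observation carried forward", with the intention-to-treat principle given as the reason. The planned comparison is a two-sample t-test or chi-square test.
- **Timing (Primary outcomes), for the PSQI:** "It will be administered at baseline and 8 weeks (at the end of the intervention". Table 1, Secondary outcomes and Data management give the same two time points for SAS, SDS and SF-36. Only the blinding question is also put at week 4.
- **Follow-up after withdrawal (Discontinuation):** "The participants who are withdraw from the trial will still be followed up and complete the assessments of primary and secondary outcomes".
- **Sample size:** "Sample size estimation was based on changes in the Pittsburgh Sleep Quality Index (PSQI) score", with a "mean difference in the PSQI of 2.0 with a standard deviation of 4.36 between the two groups". The section says "we assume a significance level α of 0.05 and power (1-β) = 0.90", arrives at 202, and then: "Considering the expected dropout rate of 20%, this study will require at least 252 participants".

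**The concern.** LOCF needs an intermediate value to carry. Here there is none, so a participant without a week-8 PSQI can contribute only the baseline score, and the change is set to zero whatever happened during treatment. Intention-to-treat settles who is analysed and in which arm. It does not justify a particular value for an unobserved outcome.

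Two things are at stake. First, the dropout allowance and the analysis describe different data sets. The allowance treats dropouts as lost and completers as carrying the full difference, whereas the analysis keeps the dropouts and gives them no effect. Secondly, the Discussion itself accepts that sham acupuncture may improve sleep. When both arms improve, setting missing participants to zero change penalises whichever arm has more of them. Unequal missingness therefore moves the treatment contrast, even when there is no true effect. The rule applies to the primary outcome and to all three secondary efficacy scales.

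**Working it through.** **Inputs from the protocol article.** Difference 2.0, SD 4.36, α 0.05 two-sided ("All planned tests are two-tailed"), power 0.90, 202 evaluable, 20% dropout, 252 randomised 1:1, so 126 per arm.

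**Assumptions, because the article gives no figures.** Mean improvement in each arm, and how missingness splits between arms. The 4.36 is taken as the within-arm SD of change, since the sizing is stated to be on changes.

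**Step 1: reproduce the plan's figures.** The noncentral t calculation gives power 0.9005 with 101 per arm and 0.8976 with 100, so 202 in total is right. Then 202 / 0.80 = 252.5, against 252 stated, which is a rounding matter. In reverse, 252 × 0.80 = 201.6. The 252 thus gives 90% power if about 202 participants are analysed at the full 2.0 points.

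**Step 2: expected difference under the stated rule.** With a proportion d missing in each arm, and missing participants who would otherwise have had the completers' effect, the analysed difference is (1 − d) × 2.0. At d = 0.20 this is 0.80 × 2.0 = 1.6.

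**Step 3: power with all 252 analysed.** Within an arm whose completers improve by m, the variance of change after imputing zeros is (1 − d) × 4.36² + d(1 − d) × m². For d = 0.20 this is 15.21 + 0.16 m². Worked case, sham 3 and manual 5: variances 16.65 and 19.21, SE = √((16.65 + 19.21)/126) = 0.533, and 1.6/0.533 = 3.00, giving power 0.848.

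| Assumed improvement, sham / manual | Power at 20% missing | Power at 10% missing |
|---|---|---|
| 0 / 2 | 0.894 | 0.928 |
| 2 / 4 | 0.870 | 0.918 |
| 3 / 5 | 0.848 | 0.909 |
| 4 / 6 | 0.820 | 0.898 |
| 5 / 7 | 0.786 | 0.883 |

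At 5% missing, power is 0.92 to 0.94 over the same range. With the SD simply held at 4.36, power at 20% missing is 0.83, and about 314 analysed participants would be needed to detect 1.6 with 90% power. If week-8 scores rather than changes were compared, power at 20% missing would be about 0.72 to 0.87, for an assumed baseline SD of 2.5 to 4.36 and sham improvement of 5 to 0.

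**Step 4: unequal missingness.** The analysed contrast is (1 − d_manual) × m_manual − (1 − d_sham) × m_sham.

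- *No true effect, both arms improve 4 points, 15% (manual) vs 25% (sham) missing:* 0.85 × 4 − 0.75 × 4 = 0.4. The variances are 0.85 × 19.01 + 0.1275 × 16 = 18.20 and 0.75 × 19.01 + 0.1875 × 16 = 17.26, so SE = √(35.46/126) = 0.530. The rejection probability is Φ(0.754 − 1.96) + Φ(−0.754 − 1.96) ≈ 0.117, or about 12% against a nominal 5%.
- *The same with a 2-point improvement in both arms:* a spurious 0.2 points and a type I error of about 6.8%.
- *True improvements 6 vs 4 (effect 2.0):* with 25% vs 15% missing the contrast is 4.5 − 3.4 = 1.1. With 15% vs 25% it is 5.1 − 3.0 = 2.1.

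**The case against.** The strongest reply is that the Discontinuation section commits the team to assessing participants who withdraw, so the share with no week-8 value may be well below 20%. That stands. The rule affects only those whose week-8 value is actually missing, and at 10% or less the power loss is small or absent.

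The power figures also depend on mean changes that the article does not give. With no sham improvement the loss at 20% missing is under one percentage point. Likewise, no differential dropout is planned or predicted, participants are blinded, and both arms have the same schedule. The type I error figures show what the rule can do and are not a forecast. With equal missingness and the same effect in those missing, the rule dilutes the effect towards the null.

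Two stronger readings are tempting, and the article does not support them:

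- *Real week-8 data from withdrawn participants would be overwritten.* The rule replaces missing data. A value collected under Discontinuation is not missing, so the two sections are compatible, although the article would be clearer if it said so.
- *The standard error is wrong because imputed values are treated as known.* A null simulation with 20% missing in both arms and both arms improving 4 points gave 4.96% rejections, with a mean estimated SE of 0.530 against an empirical 0.527. The excess rejections in Step 4 come from a shifted mean.

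Nor is this a detail left to a statistical analysis plan. The article names LOCF as the method.

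**Conclusion.** The point holds, with conditions. What follows from the text alone is that LOCF here is baseline carried forward, and that this does not match a dropout allowance that assumes dropouts leave the analysis.

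At the article's own 20%, taken as missing week-8 values equally in both arms, and with those participants otherwise having the completers' effect, the expected difference is 1.6 and the stated 90% power is not delivered. The size of the shortfall rests on assumed mean changes. A reader might infer that the trial is underpowered whatever the missingness, but the calculations at 5% and 10% do not support that.

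The bias from unequal missingness is the more serious part, because it can favour either arm and can raise the false-positive rate. It needs missingness that differs by arm together with improvement in those who are missing. It is absent only if participants with missing values truly did not change, which the article does not claim. Since the primary test and every secondary efficacy scale are affected and the remedy is a change of wording, it should be corrected.

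**What to change.** In Statistical analysis:

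1. Remove LOCF as the primary method.
2. State that week-8 data collected after withdrawal, as Discontinuation provides, are used as observed.
3. Handle week-8 values that are still missing with a missing-at-random method, for example multiple imputation within arm from the baseline PSQI, SAS, SDS and SF-36. The detail can go in the statistical analysis plan.
4. Keep baseline carried forward as a sensitivity analysis only, labelled as such.

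If LOCF stays primary, Sample size should say that at 20% missing the expected difference is 1.6 and the 90% power is not delivered, and should give the power range together with the mean changes assumed for it.

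The cost is modest extra analysis work, with no added patients or visits. The missing-at-random assumption cannot be verified from the data, which is one reason to retain a sensitivity analysis. The change should be made before unblinding.

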### Randomization and allocation concealment

A simple randomization method will be used in this trial. A total of 252 participants will be randomly assigned to either the manual acupuncture group (*n* = 126, expected) or sham acupuncture group (*n* = 126, expected) after the baseline assessment. The randomization sequence will be generated using Statistical Analysis Software 9.1 by a research assistant who will be blinded to the recruitment of participants. Randomization numbers will be sealed in a computer-generated randomization-based opaque envelope. Only the screening sequence number will be printed on the envelope. The researcher, who screens the eligible patients after baseline assessment, will separate the envelopes, and then assign the patient to the manual acupuncture group or sham acupuncture group.

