#### Secondary outcomes

Secondary outcome measures refer to scores on the SAS, SDS, and Medical Outcomes Study 36-Item Short-Form Health Survey (SF-36), which will be assessed at baseline and 8 weeks (at the end of the intervention).

Psychological symptoms, including depression and anxiety, will be assessed using the SAS and SDS. The SAS is applicable to adults with anxiety symptoms and has a wide range of applications. The SDS can fairly directly reflect the subjective feelings of patients with depression and their changes in treatment. A higher total score indicates more severe anxiety and depression [20].

Quality of life will also be assessed as a secondary outcome, using the SF-36, which includes 36 items comprising eight categories: functional capacity (ten items), physical aspects (four items), pain (two items), general health status (five items), vitality (four items), social aspects (two items), mental health (five items), and a question comparing current health conditions with those from a year ago. The total scores range from 0 to 100. Higher scores indicate better health status [21].

Blinding success rate. All patients will undergo the blinding test twice, once each at 4 weeks and 8 weeks, to assess the success rate of participant blinding. The question “When you volunteered for the current trial, you were informed that you have an equal chance of receiving either manual acupuncture or sham acupuncture. Which one do you think you received?” will be asked to them. Patients will have the choice of answering with one of the following responses: manual acupuncture treatment, sham acupuncture treatment, or uncertain.

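### The four outcome scores are compared with a t-test that ignores their baseline values; baseline-adjusted ANCOVA would gain precision, by an amount ranging from near zero to substantial

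*Protocol article*

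**What the plan says.** The Statistical analysis section of the protocol article names one family of between-group comparisons: a two-sample t-test, or for categorical data a "chi-square test will be used to test differences between the manual acupuncture group and sham acupuncture group using SPSS 19.0". It mentions no covariate or model.

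The Sample size section rests on the same unadjusted comparison, "using two-sided, two-sample *t*-tests assuming equal variance", with the inputs "there was a mean difference in the PSQI of 2.0 with a standard deviation of 4.36 between the two groups" and "we assume a significance level α of 0.05 and power (1-β) = 0.90". It opens with "Sample size estimation was based on changes in the Pittsburgh Sleep Quality Index (PSQI) score". The analysis section does not say whether the t-test is run on the week-8 score or on the change.

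All four scores have a baseline value. Primary outcomes says this for the PSQI, Secondary outcomes says it for the SAS, SDS and SF-36, and Table 1 shows the same schedule. On allocation, the article says "A simple randomization method will be used in this trial", with no stratification by baseline severity.

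**The concern.** When a continuous score is measured before and after treatment, part of the variation in the final score can be predicted from the baseline. A t-test on week-8 scores leaves that part in the error term. A t-test on change subtracts baseline with a fixed coefficient of 1, which is rarely the best weight. ANCOVA estimates the weight from the data.

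With simple randomization, the arms can also differ by chance in baseline severity in the trial as realised. Neither t-test adjusts for such a difference with the right weight; ANCOVA does.

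The two t-tests can also give different estimates and p-values. ANCOVA makes that choice irrelevant: with baseline in the model, the treatment estimate is the same whether the response is the week-8 score or the change.

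At stake are the width of the confidence interval and the power margin. The validity of the trial is not in question.

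**Working it through.** **Inputs from the protocol article:** difference 2.0, SD 4.36, two-sided α 0.05, power 0.90, 202 evaluable (101 per arm), 20% dropout, 252 randomized.

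**Inputs assumed, because the article does not give them:** the correlation r between baseline and week-8 score, 0.3 to 0.7; the ratio k = baseline SD / week-8 SD, 0.6 to 1.

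**Step 1: reproduce the plan's figure.** The exact (noncentral t) calculation at effect size 2.0/4.36 gives 100.84, so 101 per arm and 202 in total, as stated. Power at 101 per arm is 0.9005. For dropout, 202/0.8 = 252.5, which agrees with the stated 252 apart from rounding.

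**Step 2: ANCOVA against a t-test on week-8 scores.** The variance ratio is 1 − r². Taking 4.36 as the SD of the week-8 score, the residual SD is 4.36·√(1 − r²).

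| r | variance ratio | residual SD | power, 101 per arm |
|---|---|---|---|
| 0.3 | 0.91 | 4.16 | 0.925 |
| 0.5 | 0.75 | 3.78 | 0.963 |
| 0.7 | 0.51 | 3.11 | 0.995 |

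**Step 3: ANCOVA against a t-test on change.** The variance ratio is (1 − r²)/(1 + k² − 2rk). Only at k = 1 does it reduce to (1 + r)/2. For example, at k = 0.8 and r = 0.5 it is 0.75/(1 + 0.64 − 0.80) = 0.75/0.84 = 0.89. Taking 4.36 as the SD of change, the residual SD is 4.36·√ratio.

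| k | r | variance ratio | power, 101 per arm |
|---|---|---|---|
| 1.0 | 0.3 | 0.65 | 0.980 |
| 1.0 | 0.5 | 0.75 | 0.963 |
| 1.0 | 0.7 | 0.85 | 0.940 |
| 0.8 | 0.3 | 0.78 | 0.956 |
| 0.8 | 0.5 | 0.89 | 0.930 |
| 0.8 | 0.7 | 0.98 | 0.906 |
| 0.6 | 0.3 | 0.91 | 0.925 |
| 0.6 | 0.5 | 0.99 | 0.904 |
| 0.6 | 0.7 | 0.98 | 0.906 |

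**Step 4: direction of the change-score correction.** The slope of week-8 on baseline score is r/k. Subtracting baseline over-corrects only if r/k is below 1. At k = 1 and r = 0.5 the slope is 0.5, so change over-corrects. At k = 0.6 and r = 0.7 it is 0.7/0.6 = 1.17, so change under-corrects.

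**Step 5: size of chance imbalance.** Assume a baseline PSQI SD of 2.5 to 4.36. The standard error of the baseline difference is SD·√(2/101) = 0.35 to 0.61, so its 95% range is ±0.69 to ±1.20 points. With a slope of 0.5, a difference at that limit would shift a week-8 comparison by 0.34 to 0.60 points, against a target of 2.0. This is an extreme case, and the t-test's standard error already allows for it.

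**The case against.** The strongest reply is that nothing is broken. In a 1:1 randomized trial the unadjusted t-test is unbiased over randomizations and keeps its type I error. The analysis and sample size sections agree with each other, and 90% power is met on the stated inputs. All of this stands. A reader might infer from simple randomization and the missing covariate that the estimate will be biased or the trial underpowered. The article supports neither: chance imbalance is part of the sampling error that the t-test's interval already reflects, and the power figure reproduces.

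Second, the gain is uncertain where it matters most. The sample size text points to change scores, and there the gain depends on k as well as r. Entry requires diagnosed insomnia, which may narrow the baseline spread of the PSQI and bring k below 1. This stands too. It would be tempting to say that the t-test costs a third more patients (1/0.75 = 1.33). Against change scores, that figure belongs to one point, r = 0.5 with k = 1. Nor can one say without condition that a change score over-corrects, as Step 4 shows.

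Third, the power figures use 101 evaluable per arm, whereas the plan carries the last observation forward for dropouts. With assessments only at baseline and week 8, the carried value is the baseline, which would alter r, the SDs and the effect. The figures above do not model this and are indicative only.

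Fourth, leaving open whether week-8 score or change is tested may be detail kept for an analysis plan that is not shown. That is fair, and the point does not rest on it. The unadjusted test itself is fixed in two sections and so is a stated choice.

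**Conclusion.** The point holds as an efficiency improvement that should be made. The planned t-test is valid and adequately powered on the article's own inputs, but it does not use the baseline value efficiently and does not properly adjust for chance baseline differences in the realised trial.

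For r between 0.3 and 0.7 and 101 per arm, the gain over a week-8 t-test is clear: power 0.93 to 0.995 instead of 0.90. Over a change-score t-test, power would be 0.94 to 0.98 if the baseline and week-8 SDs are equal, and 0.90 to 0.96 if k is 0.6 to 0.8, so that gain runs from near zero upward. Both r and k are assumptions. ANCOVA is at least as precise as either t-test at every value examined; only the size of the gain is in doubt.

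**What to change.** State in the Statistical analysis section that the primary analysis is an ANCOVA of week-8 PSQI total on treatment arm and baseline PSQI, reported as the adjusted mean difference with its 95% confidence interval. Use the same model for SAS, SDS and SF-36, each with its own baseline value. Keep the t-test as a supportive analysis, and say whether it is run on the week-8 score or on change. Leave the sample size at 252.

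The cost is one or two sentences, settled before unblinding. The baseline data are already being collected, and the planned software can fit the model.
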